**Abstract*:**

After more than 20 years of studies on the mother-to-child transmission and the therapy strategies against hepatitis B virus (HBV) infection, we have known that the HBsAg/HBeAg and HBV DNA level are the predominant factors related to the HBV intrauterine infection. The present project will prospectively investigate the effect of tenofovir disoproxil fumarate (TDF), a nucleotide analogue against viral infection, in blocking the HBV vertical transmission and the potential mechanism involved in this process among the pregnant women who are HBsAg/HBeAg-positive with high viral loads. The trial will be randomly designed. We will check the efficacy and rationality of the TDF in blocking the mother-to-child transmission of HBV infection (primary outcome). We will dynamically monitor the HBsAg/HBeAg, HBV DNA levels (secondary outcome) and liver function of the women during the pregnancy and the hepatitis B parameters, HBV DNA level (secondary outcome) and liver function of infants immediately after the birth and at age of 7 months. The ratio of T lymphocytes and cytokines level in the serum related to the HBV infection will also be checked (before TDF intervention, before and after delivery, etc) to reveal the effect of TDF on the immune function of the pregnancies, which will help to determine whether the changes of immune system by TDF contribute to the block of vertical transmission of HBV. The known and/or potential mutation site(s) of genes related to the drug resistance or tolerance will be examine by PCR in the pregnancies after TDF treatment, which will facilitate the subsequent therapy against chronic HBV infection. The infants from TDF treated mothers will be followed up till 2 years old and monitor the growth curve and IQ value. In summary, the present study will allow us to evaluate the efficacy and safety of TDF in the pregnancies and to provide the evidence of TDF against HBV during the pregnancy.

*** Since the original protocol was wrote in Chinese and there are too much contents, I try my best to translate the key points of the protocol into English.**

**INTRODUCTION:**

Hepatitis B virus (HBV) infection is a main problem for the public health, particularly, in the endemic regions, such as in China. It is estimated that 9.9% of the population in China are HBV carrier and that approximately 120 millions of patients are chronic HBV infection. The mother-to-child transmission is considered as the main cause of chronic HBV infection, which can occur in the utero, during child birth, and postpartum.

The application of hepatitis B vaccine and hepatitis B immunoglobulin (HBIG) effectively blocks the infant infection during the delivery process and postpartum after the birth from the HBsAg-positive mother. But it has no effect on the intrauterine infection that contributes to 5-8% of HBV infection. However, with the improvements of the research methods and detection sensitivity, the intrauterine infection has been shown to contribute to 40-60% of the HBV infection. It believes that the chronic HBV infection still occurs in 5-15% of infants born to the HBeAg-positive mother even regular immunoprophylaxis is given. Therefore, the intrauterine HBV infection is still one of the important reasons for the immunoprophylaxis failure. Thus, it is critical to block the intrauterine infection in order to control the hepatitis B epidemic and to prevent the HBV-related diseases in China and worldwide.

Ten years ago, multiple injections of HBIG was used in the pregnant women at the late gestation to block the mother-to-child transmission of the HBV infection. But the effect is not clear and the guidelines are no longer recommended. Nowadays, no available guideline is used around the world to block HBV intrauterine infection during the pregnancy. The studies have demonstrated that HBV DNA and HBxAg are high risk factors for HBV intrauterine infection. So, control of the HBV DNA levels and the HBXAG expression will be expected to attenuate HBV intrauterine infection.

The nucleoside analogues (NAs) have been widely used against viral infection such as HIV and HBV. The NAs play their roles by mimicking the structure of nucleotides, but do not function as the nucleotides. Therefore, the NAs incorporate into HBV DNA during the process of DNA synthesis and synthesize the non-function nucleic acid chain, leading to the termination of the replication of hepatitis B virus. Among the NAs, lamivudine and Biff have higher incidence of drug resistance; the antiviral effect of adefovir ester is weaker; entecavir and tenofovir have stronger antiviral effect with the lower resistance rate. Based on the safety for the pregnancy, the FDA of USA categorizes tenofovir and Biff as "B" class reagents, since their safety have been approved in the animal model but limited data in the human application. The animal study also shows that lamivudine, adefovir and entecavir result in teratogenic embryo. Thus, they are categorized as "C" class reagent by the FDA, although no data from humans for these medicines. In addition, the global multicentre clinical trial and clinical study in China have shown that the application of lamivudine at late stage of gestation can inhibit the HBV replication, reduce viral load in the pregnant women, recover ALT and HBeAg to the normal level, thus decrease the intrauterine infection of HBV. However, lamivudine is confirmed to have high risk in inducing viral mutation and belongs to the "C-class" medicine for the pregnancy, thus generally it is not recommended for the pregnant women. The study on the use of adefovir ester in the pregnant women is inadequate.

Tenofovir (tenofovir disoproxil fumarate, TDF), a new type of nucleotide reverse transcriptase inhibitors, is effectively against a variety of viruses therefore used for the treatment of viral infectious diseases. The TDF component tenofovir diphosphate inhibits the viral polymerase by competitively combining with the substrate of natural deoxyribose. As mention above, it can also terminate the DNA chain synthesis by inserting into DNA chain. The in vitro studies have shown that TDF is effective against a wide range of viruses including the strains that are resistant to nucleoside reverse transcriptase inhibitors. Van Bommel reported that 10 patients, who were chronic HBV infection and tolerated to lamivudine (LAM) and subsequent adefovir therapy, have been treated only with TDF for more than 12 months and no drug resistance was found in all those patients, suggesting that unique TDF treatment has significant antiviral effect, particularly, for the patients tolerating to the other NAs medicines.

As a “B” class medicine, the TDF has been approved for its safety and efficacy in primates. Until today, there is only one report about its effect on the intrauterine HBV infection. In this study with small sample size (8 subjects), the pregnant women accepted 300mg/day TDF orally. Among those patients, one case was pregnant during TDF treatment; 3 individuals took TDF to control active hepatitis; 4 patients were given TDF to prevent intrauterine HBV infection. All those patients continued to accept TDF therapy after the delivery. Their results showed that patents’ HBV DNA levels decreased 2-4 log10 copies/mL in the first 4 weeks and were less than 10^4^ copies/mL after the delivery. They suggested that the application of TDF at late stage of the gestation was safe and did not induce the drug resistance. In addition, given that the TDF efficiently inhibits the viral DNA replication with limited kidney cytotoxicity, more and more studies focus on the TDF antiviral treatment in the pregnancies at late stage of gestation. Indeed, compared to other NAs, TDF has not been reported for the drug resistance even after 3 years treatment. However, more studies with large size of the subjects and longer duration of follow-up are necessary to further confirm the safety and efficacy of TDF in pregnant women.

**HYPOTHESIS**

Based on the evidences described above, the TDF effectively inhibits the HBV replication with less renal toxicity. Particularly, it is also effective in the patients tolerating to other NAs treatment and no drug resistance is reported. Intriguingly, the TDF has been tested in the pregnancies at the late stage of gestation against HBV infection. However, the prospective studies with large sample size and control populations are lacked to confirm definitely the safety and efficacy of TDF on the pregnant women and infants.

Therefore, the present trial is designed to prospectively investigate the effect of TDF in the pregnancies. The pregnant women will be randomly grouped into TDF treatment and control subjects. To test its maximal effect, the patients who are HBsAg/HBeAg positive with high viral burdens will be selected, since, as mentioned above, the HBxAg and HBV DNA levels are closely associated with intrauterine HBV infection. On the other hand, the application of TDF at late stage of the gestation might be too late to block intrauterine HBV infection, particularly, in the pregnancies who are HBsAg/HBeAg-positive with high viral burdens. Thus, we propose to give TDF treatment at the mid stage of gestation (24 weeks) to inhibit the intrauterine infection by HBV.

**STUDY OBJECTIVES**

The present prospective study aims at investigating the effect of TDF against the mother-to-child transmission of HBV infection. Through this trial, we will:

(1) confirm the efficacy of TDF in blocking HBV intrauterine infection during pregnancy;

(2) monitor the effect of TDF on the dynamic changes of HBV DNA levels in the pregnancy;

(3) test the HBsAg and HBeAg expression during and after the TDF treatment;

(4) screen the changes of HBV resistance genes related to the NAs treatment in the pregnant women with chronic HBV infection;

(5) clarify the adverse effects induced by TDF treatment during the pregnancy for both mother and infants.

This clinical project will allow us to better understand the safety and efficacy of TDF against HBV infection during the pregnancy. It will also help in clarifying the potential adverse effects of this medicine. The study will also provide the evidence to further optimize and to facilitate the TDF application in blocking the vertical transmission of HBV infection.

**INTERVENTION**

The TDF is manufactured as tablet and will be taken orally. The dose will be 300mg/day.

The therapy will be performed in three hospitals of China (The First Affiliated Hospital of Medical College of Xi’an Jiaotong University, Shaanxi Provincial People Hospital and Maternal and Child Health Care Hospital of Xinjiang Uygur Autonomous Region). The study will last for 4 years from January 2013 to December 2016.

The TDF therapy will be started at 24 weeks of gestation. To evaluate the effect of TDF, the blood sample will be collected in all the pregnancies with/without TDF treatment before initiating the TDF therapy, then every 4 weeks till just before delivery. After delivery, this procedure continues till 28 weeks postpartum. After collecting the blood, the parameters related to live function and HBV infection will be checked within 24h. The aliquot of blood will be used to extract DNA using DNAout kit to check the expression of HBxAg and the mutation of drug resistant genes. The left will be used to harvest serum. In brief, the blood will be kept in ice for 30min before the centrifugation. The serum will be aliquoted and kept at 80°C for the further analysis. All sample tubes will be labelled with the case number of patient.

**STUDY DESIGN**

A random study will be designed to investigate the effect of TDF in blocking vertical transmission of the HBV infection.

Before starting the trial, we estimate the sample size using online sample size calculator for two parallel-sample proportions (http://clincalc.com/stats/samplesize.aspx). According to the literatures, we learn that after routine immunoprophylaxis the mother-to-child transmission of HBV infection is around 10-30% (we proposed as 30% for the calculation). We expect the TDF treatment will reduce the infection to 5-10% (we perform calculation as 5%). The superiority margin is supposed to be 0.05. So, we have an estimated samples size with equal allocation as 35 for each group. The present trial will collect 60-80 individuals for each group.

We will randomly allocate patient number into TDF and control group based on the random number table. The patients for the study will be selected as shown in the bellowing flow chart. When the pregnant women visit the hospital for the first time, generally, the routine care will be given and the laboratory parameters of blood sample including blood cell counts, HBV parameters, liver function, kidney function, etc. will be checked. The ultrasound of foetus will also be performed. Based on the laboratory data and history, the non-eligible pregnancies will be excluded. The eligible pregnant women will be further selected according to the criteria. Then, the final enrolled pregnancy will be numbered as the visiting order. This patient number will be corresponded to the allocated number from random number table.

During the study, the patient will be excluded if special situation occurs including preterm delivery, lost follow up or any other severe side effects.

[figure not shown]

- Subject:

According to our experiences, it is estimated that around 80-150 pregnancies with HBV infection will visit our hospitals. Three hundred to 500 HBV-infected pregnant women totally will be predicted in 3-4 years.

- Eligibility criteria

20-35 years old pregnant women with the HBV infection.

- Inclusion criteria

The pregnancies who are HBeAg/HBsAg double positive as well as serum HBV DNA≥2×106 (6.3 log10) IU/mL.

- Exclusion criteria

① co-infection with HIV, HCV or HDV; ② HBV treatment history within 6 months; ➂ abortion history or clinical manifestation of inevitable abortion; ④ congenital deformity of foetus; ⑤ hepatocellular carcinoma evidence, renal or hepatic dysfunction, creatinine clearance rate <100mL/min, alanine aminotransferase (ALT) >5 times of upper limit of the normal level, bilirubin >2mg/dl; ⑥haemoglobin <8g/100mL, neutrophil <1000/mm^3^, albumin <2.5g/100mL; ⑥ special medicine treatment during the pregnancy; ⑦ biological father of infant has chronic HBV infection.

- Randomization

Based on our prediction, less than 50 pregnancies per year are eligible for the study. To ensure the similar number for treatment and control group, we estimate that minimal 30 subjects can participate in the study (total around 120 subjects). When getting 120 subjects, the enrolment will be stopped.

In random number table, we randomly start and separate 3 digital number as group following the order in number table. The separated number are written on the paper following the order of the random number table. The repeated number and number big than 120 will be excluded. The first 60 number based on the order will be allocated as TDF treatment. The left will be controls.

- Conceal the intervention

The selected number and corresponding intervention will be hided in the individual envelope and sealed. On the surface of the envelop, the selected number is written. Then the envelops are managed in order (from 001 to 120) and given to the doctor when having the enrolled subject (visiting order).

- Ethics

We have got the approval from the hospital for the study (approval N° 2012-136). The consent will be prepared and printed. The patients will be informed and sign the written consent.

- Potential benefit to the subjects

The TDF therapy in the HBV-infected pregnant women with high viral loads will help in reducing the risk of mother-to-child transmission. It will also protect mothers during the gestation periods due to the special immune situation. In addition, it will help to understand the safety and efficacy of TDF in blocking the vertical transmission, its effect on mothers and infants and potential adverse effects, which will facilitate the TDF treatment in the pregnancies in clinic.

- Potential risk

The most potential risk for the trial is the side effects of TDF, such as preterm delivery and severe adverse effects including dysfunction of liver and kidney as well as the HBV resistance to TDF treatment. The trial has no apparent physical, psychological and economic effect. The pregnancies will not have any stress or discomfort when answering the question or focusing on the research. The participants will face the same stress as other pregnancies when collecting blood routinely.

- Methods to protect the privacy, data and right of subjects

Before starting the trial, the participants will be informed, agree and sign the printed consent. All the personal information will be confidential. A person will specifically manage the collected data that will be saved in the computer with password. Only this person can access the computer.

- Intervention

The TDF therapy will be given to the pregnant women who are HBsAg/HBeAg-positive with high viral burdens. The details of the medicine will be concealed. The pregnancies will take the medicine orally, 300mg/day, starting the date of enrolment (24 weeks of gestation) until 4 weeks postpartum. This dose is recommended by the manufacture and also used by most of the studies. The method used for assigning subjects to the treatment group is described above in the section of randomization.

The medicine will be distributed to the participants every time when visiting the doctor. The medicine will be prepared and packaged in the pharmacy centre of the hospitals.

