**STATISITICAL ANALYSIS**

- All data will be collected together to the person who is in charge of data collection. The data will be save as Excel file format.
- When the study is finished, we will discuss with statistician from the host university in managing and analyze the data.
- The data will be presented as mean±SE and SPSS18.0 (SPSS inc., Chicago, USA) will be used for the analysis. Baseline characteristics and safety outcomes will be compared between the TDF treatment and the controls using t-tests for continuous variables and chi-square tests or fisher exact tests for categorical variables. The Mother-to-child transmission rate and the recovery levels of the HBV DNA 28 weeks after the delivery between the two groups will be compared by Fisher exact tests. A mixed model, repeated measures analysis for variance will be used to analyze if the serum HBV DNA levels change differently with or without TDF treatment. The planned contrasts will be tested for the "change in HBV DNA for each group between baseline and delivery time" and "differences from weeks to the weeks’ within TDF treatment group. The p value less than 0.05 will be considered as statistically significant.
- All data will be confidential during and after the study. The data will be transferred and stored in the server of the hospital. Special authorization is needed to access these data after the closure of the study.

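### The sample size pairs the most favourable ends of both planning ranges; at 60 per group Fisher's test has 80% power only for about 24% vs 5% (or 32% vs 10%), and Boschloo's exact test would recover some of the lost power

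*Protocol*

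**What the plan says.** The sample-size paragraph of STUDY DESIGN gives two ranges and takes one end of each. For controls, transmission after immunoprophylaxis "is around 10-30% (we proposed as 30% for the calculation"; for treated women, TDF is expected to "reduce the infection to 5-10% (we perform calculation as 5" (per cent). It adds "The superiority margin is supposed to be 0.05" and concludes "So, we have an estimated samples size with equal allocation as 35 for each group". It then plans 60-80 per group. The Randomization item stops enrolment at 120 and assigns 60 numbers to TDF and the rest to control, so the achievable size is 60 per group.

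The INTRODUCTION gives another background rate: "the chronic HBV infection still occurs in 5-15% of infants born to the HBeAg-positive mother even regular immunoprophylaxis is given". The inclusion criterion is narrower than that population: "The pregnancies who are HBeAg/HBsAg double positive as well as serum HBV DNA" at or above 6.3 log10 IU/mL.

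The statistical analysis section names Fisher's exact test for the transmission rate and states "The p value less than 0.05 will be considered as statistically significant". Neither power nor sidedness is stated.

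**The concern.** The highest control rate and the lowest TDF rate together give the smallest sample size that the two ranges allow. No figure makes 30% the expected control rate or 5% the expected TDF rate. The 30% is also twice the top of the INTRODUCTION's 5-15%, although that figure describes a broader group of mothers.

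If the true rates lie elsewhere in the Protocol's own ranges, a non-significant primary result becomes likely even when TDF works as expected. The trial's first objective is to confirm efficacy, so readers could take such a result as evidence of no effect. Fisher's test adds to the problem: with small counts it is conservative and gives up power that the 5% level would allow.

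**Working it through.** **Inputs.** Control rate 30% (range 10-30%), TDF rate 5% (range 5-10%), equal allocation and significance level 0.05, all from the Protocol. Two-sided testing and 80% power are assumptions, chosen because they reproduce the stated size.

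**Reproducing 35.** Pooled-variance formula without continuity correction:

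n = [z(0.975)·√(2·p̄·(1−p̄)) + z(0.80)·√(p1(1−p1) + p2(1−p2))]² / (p1−p2)²

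With p1 = 0.30, p2 = 0.05 and p̄ = 0.175:

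- 1.96 × √0.28875 = 1.053
- 0.842 × √0.2575 = 0.427
- (1.053 + 0.427)² / 0.0625 ≈ 35.06

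This matches the stated 35 (36 if rounded up). At 90% power the formula gives 47. A true superiority margin of 0.05 would give 51 (unpooled, 80% power). The 35 therefore reproduces only if the 0.05 is read as the significance level.

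**Same formula at other pairs within the stated ranges, 80% power, per group:** 30 vs 10: 62; 20 vs 5: 76; 15 vs 5: 141; 20 vs 10: 199; 10 vs 5: 435.

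**Exact power at 60 per group.** Power = Σ P(X1 = i)·P(X2 = j), summed over all tables (i, j) that the test rejects, with X1 ~ Bin(60, p1) and X2 ~ Bin(60, p2). Fisher rejects when its two-sided p is at or below 0.05. Boschloo uses the Fisher p as its test statistic and raises the cut-off as far as the maximum size over all common rates allows. At 60 per group the cut-off is 0.0665, with maximum size 4.9%. Fisher's own maximum size is 3.5%.

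| Control vs TDF | Fisher | Boschloo |
|---|---|---|
| 30% vs 5% | 95% | 96% |
| 25% vs 5% | 85% | 87% |
| 30% vs 10% | 73% | 77% |
| 20% vs 5% | 63% | 68% |
| 15% vs 5% | 33% | 39% |
| 20% vs 10% | 25% | 29% |
| 10% vs 5% | 9% | 13% |

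**Smallest control rate with 80% Fisher power at 60 per group.** Against 5%: about 24% (power 81%), a drop of 24 − 5 = 19 points. Against 10%: about 32%, a drop of 32 − 10 = 22 points. The second lies outside the stated 10-30% control range.

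**Losses.** STUDY DESIGN removes preterm deliveries and women lost to follow-up, and states no dropout rate. If 50 per group remained (an assumption), Fisher power would be 90% for 30 vs 5, 51% for 20 vs 5 and 24% for 15 vs 5.

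**The case against.** **The size was raised well above 35.** This stands. A reader might infer that the trial can answer its question only for a 25-point drop, because the calculation used 30% vs 5%. That is not so. The 25-point drop is what 35 per group was sized for. With 60 per group, Fisher power is 85% for 25 vs 5 and 81% for 24 vs 5. The Protocol does not explain the increase, and the 120 cap rules out the upper figure of 80 per group, at which Fisher power would be 87% for 30 vs 10 and 79% for 20 vs 5.

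**The two background rates describe different things.** This also stands. A reader might infer that 5-15% contradicts 30%. The INTRODUCTION's figure is for chronic infection in infants of HBeAg-positive mothers with no viral-load limit. The trial enrols only women with high viral load, and its endpoint is infant HBV DNA above 20 IU/ml or positive HBsAg at 28 weeks. The HYPOTHESIS section says high-burden women were chosen to show the largest effect. A control rate above 15% is therefore plausible, and the figures are in tension rather than contradiction. Even so, the range in STUDY DESIGN starts at 10%, and nothing in the document singles out 30%.

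**The trial does not miss a power target.** True: none is stated, and 80% is inferred.

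**Fisher's test is valid, and Boschloo's gain is modest.** Both are true. The change does not rescue 15 vs 5 or 10 vs 5. It does gain power at no cost in patients or error rate. A power table and reporting rules may sit in a SAP that is not shown, so their absence is not held against the Protocol.

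**Conclusion.** The point holds in this form. The planning rates are the most favourable ends of both stated ranges and are not justified by any figure. At 60 per group, Fisher's test reaches 80% power only from about 24% vs 5%, or about 32% vs 10%. With a control rate of 20%, the middle of the Protocol's range, Fisher power is 25% to 63% depending on the TDF rate. At 15% vs 5% it is 33%.

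The conclusion assumes two-sided testing at 5%, 80% power as the benchmark, and all 60 women per group analysed; losses would lower every figure. It does not say what the true control rate is. The documents cannot settle that, and a rate high enough for adequate power remains possible.

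**What to change.** Keep 120 women, and make three changes to the text:

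1. In the statistical analysis section, replace Fisher's test for the primary transmission outcome with Boschloo's exact test at two-sided 5%. It holds the level, is never less powerful than Fisher's, and gains 1 to 7 points over the pairs above. Derive its cut-off from the numbers actually analysed in each group.
2. In STUDY DESIGN, state what 60 per group can detect: with Fisher's test, 80% power for about 24% vs 5% or a larger difference (about 32% if the TDF rate is 10%). Give the powers across 10-30% vs 5-10%. Do not describe the trial as powered only for 30% vs 5%.
3. Report the risk difference with its 95% CI, so that a non-significant result is read against the range of effects still compatible with the data and not as no effect.

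The cost is some rewording and one test run in free software outside SPSS 18. No extra patients are needed. The Protocol will show openly that power is low over much of its own planning range.

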**STUDY PROCEDURES**

- Screening for eligibility

The participants will be screened by the consulting doctor when they visit the hospital for the first time based on the criteria. The potential eligible pregnancies will be monitored every 4 weeks till 24 weeks of gestation. According to the parameters of pregnancies at 24 weeks of gestation, the pregnant women will be enrolled or not for the study.

- Visit

The enrolled pregnant women will visit the doctor every 4 weeks till 28 weeks postpartum.

- Data collection

Routinely, when patients visit doctor for the first time, all personal information will be recorded as electronic file including birth date, home address, contact information, family condition (family members, estimated annual income, work condition, etc), health history, etc. The medical records from other hospital(s) will also be collected.

The consulting doctor will provide the prescription for the lab examination or other examination such as ultrasound and infant monitor. All the obtained results from the examination will send back to the doctor. The person who is charge of the study will record all data in the specialized computer.

- Outcomes measurement

The primary outcome is the mother-to-child transmission of HBV infection, which will be determined when the infant’s serum HBV DNA is higher than 20 IU/ml or HBsAg is positive 28 weeks after the birth.

The secondary outcome is the recovery of HBV DNA levels at 28 weeks postpartum in the pregnancies with or without TDF treatment after the cessation of TDF treatment.

- Safety and adverse event monitoring

The doctor will carefully ask the condition and situation of the pregnancies during the consultation. At the same time, the safety is also monitored by the blood assay.

Based on the severity of patients’ situation (vomit, rash on the skin, liver and kidney function, etc), the doctor will give the corresponding treatment and decide whether withdrawing the study for the patient.

The emergence contact information will be provided to the pregnancies in case needing help and suggestion from doctor as well as reporting the adverse events. All the adverse effect will be recorded till the complement of the follow-up.

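### The protocol excludes randomised women for preterm delivery, loss to follow-up or severe side effects, two of which it names as harms of TDF, so the transmission comparison is open to bias and the safety comparison may lose its events

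*Protocol*

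**What the plan says.** The exclusion rule follows the allocation text in the Protocol's STUDY DESIGN section: "During the study, the patient will be excluded if special situation occurs including preterm delivery, lost follow up or any other severe side effects". It is separate from the eligibility and exclusion criteria, which are listed afterwards.

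Four other places bear on it:

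- **Timing.** STUDY PROCEDURES, Screening for eligibility: "According to the parameters of pregnancies at 24 weeks of gestation, the pregnant women will be enrolled or not for the study". The Intervention paragraph starts TDF on the day of enrolment.
- **Harms.** Under Potential risk, the protocol says: "The most potential risk for the trial is the side effects of TDF, such as preterm delivery and severe adverse effects".
- **Objective 5.** The trial is to "clarify the adverse effects induced by TDF treatment during the pregnancy for both mother and infants".
- **Withdrawal.** Under Safety and adverse event monitoring, "the doctor will give the corresponding treatment and decide whether withdrawing the study for the patient". The same subsection also says that every adverse effect is recorded until follow-up ends.

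The primary outcome is infant infection at 28 weeks. The statistical section says that transmission rates "between the two groups will be compared by Fisher exact tests", and that safety outcomes are also compared between the groups. It names no analysis population.

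**The concern.** Randomisation makes the arms comparable only as long as the women allocated are the women compared. The rule removes women for things that happen after allocation, and the protocol itself regards two of the three reasons as possible effects of the drug. Membership of the analysed set can then depend on treatment, and a difference in transmission between the remaining women need not be an effect of TDF.

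The safety side is more direct. Preterm delivery and severe adverse effects are among the events that objective 5 needs, and they are also the reasons for exclusion. If an excluded woman is also left out of the safety comparison, her event goes with her.

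**Working it through.** **1. Do the events come after allocation?** Women are enrolled and numbered at 24 weeks, and each number corresponds to a sealed allocation. Preterm delivery, side effects and loss to follow-up in an enrolled woman therefore all come later. The rule is a post-randomisation exclusion, not an eligibility criterion.

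**2. Can treatment affect the reasons?** The protocol's own list of TDF risks contains preterm delivery and severe adverse effects. The phrase about *other* severe side effects in the rule also places preterm delivery among side effects. No placebo is described for the controls, so exclusion for side effects could fall more often on the TDF arm. That last step is an inference; the document gives no rates.

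**3. The plan's own figure.** The protocol gives 35 per group for 30% versus 5%. It states neither power nor sidedness; I assume 80% and two-sided 0.05. With the pooled formula, n = [1.96·√(2·0.175·0.825) + 0.8416·√(0.30·0.70 + 0.05·0.95)]² / 0.25² = (1.053 + 0.427)² / 0.0625 ≈ 35.1. That is 36 when rounded up, in line with the stated 35. With 60 per arm (Randomization paragraph) there is room to lose patients without losing planned power. The problem is validity, not numbers.

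**4. Effect on the transmission rate.** Let X infants of 60 in an arm be infected, and let k pairs be excluded, of whom a proportion r is infected. The rate among those retained is (X − k·r)/(60 − k). It equals X/60 only if r = X/60. With X = 6 and k = 6 (assumed):

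| Infected among the six excluded | Retained rate |
|---|---|
| 0 | 6/54 = 11.1% |
| 2 | 4/54 = 7.4% |
| no exclusion | 6/60 = 10.0% |

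The direction thus depends on a quantity that the document does not give.

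**5. Effect on the test** (two-sided Fisher exact; all event counts are assumptions):

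| TDF | Control | p | Situation |
|---|---|---|---|
| 6/60 | 15/60 | 0.053 | all randomised pairs |
| 4/54 | 15/60 | 0.013 | six TDF pairs out, two infected; no controls out |
| 4/54 | 13/54 | 0.032 | six controls also out, two infected |
| 4/54 | 12/54 | 0.055 | six controls also out, three infected |

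**6. The same at about the planning rates.** Take 3/54 versus 18/60 after six TDF exclusions, p = 0.0007. Putting the six back gives:

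| Infected among the six | TDF | p against 18/60 |
|---|---|---|
| 0 | 3/60 | 0.0005 |
| 2 | 5/60 | 0.005 |
| 4 | 7/60 | 0.023 |
| 6 | 9/60 | 0.079 |

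Here the conclusion changes only in the extreme case.

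**7. Safety.** If women with preterm delivery leave the safety set, the preterm count is 0 in both arms whatever the true rates. If they stay in it, the comparison is intact. The protocol does not say which applies.

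**The case against.** The strongest reply is that the rule does not say what the woman is excluded from. It stands in the enrolment text, and the statistical section deletes no outcomes. It may mean only withdrawal from participation, as in the monitoring paragraph. A statistical analysis plan not shown here could define an as-randomised population. This justifies saying open to bias rather than biased. It does not remove the point: withdrawal would still leave the 28-week infant test unsecured, and an as-randomised population would sit badly with the protocol's own sentence.

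Three stronger readings are tempting and are not supported:

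- A reader might infer that the rule makes TDF look better than it is. That requires excluded TDF infants to be infected more often than retained ones, and it ignores exclusions among controls. The protocol gives no such rates, and the fall from p = 0.053 to 0.013 depends on one-sided exclusions.
- A reader might infer that safety cannot be compared at all. The commitment to record all adverse effects, and the planned safety comparison, speak against that.
- A reader might infer that the doctor who decides on withdrawal knows the arm. The sealed envelope is given to the doctor, so this is plausible, but the withdrawal paragraph does not say so, and the Intervention paragraph says that details of the medicine are concealed.

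**Conclusion.** The point holds as a defect in what the protocol states, not as an omission. The exclusion rule acts after randomisation, on events that the protocol itself attributes to TDF. If it is followed as written, the primary comparison is no longer between the randomised groups.

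The direction and size of any bias in efficacy are unknown; there is none if excluded and retained pairs within each arm transmit at the same rate. With 60 per arm, six exclusions can carry a borderline result across 0.05, while a difference near the planning rates mostly survives. Both statements rest on assumed counts. The loss of safety events is conditional on excluded women leaving the safety set, and on that the exclusion rule, the adverse-event recording sentence and the statistical section have to be reconciled. Because one sentence exposes both the primary and the safety comparison and is easily changed, it should be corrected.

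**What to change.** Delete the exclusion sentence from STUDY DESIGN and state instead that:

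- every randomised mother-infant pair is analysed in its assigned arm;
- data collection, including the already scheduled 28-week infant test, continues regardless of preterm delivery, adverse events or stopping of drug;
- preterm delivery and severe adverse events are reported by arm as safety outcomes in all randomised women.

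Reconcile the withdrawal wording under Safety and adverse event monitoring with this, as far as data collection and analysis are concerned. The clinical decision itself is outside this point.

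Deleting the sentence does not recover results that were never obtained. For pairs without a 28-week infant result, report the number by arm and give sensitivity analyses, including one that counts missing as transmission in both arms. That convention penalises the arm with more losses, so it belongs among the sensitivity analyses and need not be the primary one.

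The cost is one paragraph of wording, with no added patients and no visits beyond those scheduled. The estimated effect may come out slightly less favourable.
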